### **8.2.1 Primary analysis**

The primary study objective is to compare the risks of HIV acquisition among women randomised to DMPA, LNG implant, and the copper IUD. The primary analysis will include computation of the hazard ratios of HIV seroconversion based on a proportional hazards (PH) regression model, stratified on site. Only contraceptive method group will be included in the primary stratified model. An appropriate interim spending function will be used to account for interim analyses and control the type I error for each comparison at the 0.04 level. Women will be analysed according to their randomised contraceptive method, regardless of method switching; only women who are found to have been HIV-infected at enrolment (defined by a positive HIV RNA PCR test on the archived enrolment plasma sample) or who fail to contribute a follow-up HIV test result will be excluded from the primary analysis. Women who do not HIV seroconvert during the study will have their time in analysis censored at the date of their last negative HIV test result.

### **8.2.2 Analysis of secondary endpoints**

#### **Pregnancy rates**

The study will compare the risks of pregnancy between method groups based on two-sided 95% confidence intervals for the hazard ratios of pregnancy obtained from a PH regression model, stratified by site. The study team will analyse

pregnancy rates both according to randomised contraceptive method group (primary) and restricted to periods with exposure to each contraceptive method (secondary). If too few pregnancies are observed in a particular group to justify asymptotic methods, exact log-rank tests will be used to make comparisons at the two-sided  $\alpha=0.05$  level of significance.

### **Contraceptive method continuation**

The study will summarise method continuation in frequency tables including reasons for discontinuation (e.g. refused assigned method, AE-related, participant request to stop or switch methods). The study will assess differences across randomisation groups using exact tests conducted at the two-sided 0.05 significance level. The study will compare rates of method discontinuation or switching (time to first event) between randomisation groups using two-sided, 95% confidence intervals for hazard ratios obtained from a stratified PH model. Cumulative probabilities of remaining on assigned method will be estimated based on Kaplan-Meier survival methods.

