| Population     | Sexually active, HIV-negative women, 16-35 years old, seeking effective contraception, willing to be randomised to any of the study arms, and not desiring pregnancy for the duration of study participation                                                                                                                                                                           |
| Sample size    | Approximately 7,800 women (2,600 per arm)                                                                                                                                                                                                                                                                                                                                              |
| Follow-up      | 18 months per woman or until closure of the study or study site                                                                                                                                                                                                                                                                                                                        |
| Study Sites    | Approximately 12 sites in Eastern and Southern Africa                                                                                                                                                                                                                                                                                                                                  |
| Study Duration | Enrolment will require an estimated 18 months. Total duration of the study will be approximately 36 months from first enrolment.                                                                                                                                                                                                                                                       |
| Operations     | The study team, in coordination with the funders and the Data and Safety Monitoring Board, will define key metrics and a priori criteria for stopping the trial or individual arms for operational futility as part of trial design, including % of women willing to be randomised, accrual rate, % of women discontinuing methods post-randomisation, and % loss to follow-up. |

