The estimated trial size is defined by the target of observing at least 250 incident HIV infections for each pairwise comparison, to achieve 80% power to detect a 50% increased risk with a two-sided type I error of 0.04. This calculation allows for up to 10% dilution of treatment effect due to loss of person time on allocated contraceptive method, e.g., method discontinuation. The total numbers of enrolled participants and HIV seroconversion events necessary to achieve these pairwise event totals will depend on the patterns of risk across the methods, the underlying incidence rate in the study population, and the outcome of monitoring procedures designed to drop one or more arms if there is compelling interim evidence of increased risk or lack of effect among the various methods. These considerations will be reviewed by the DSMB on an on-going basis. Taking into account this uncertainty, a total cohort size of approximately 7,800 has been selected, assuming an underlying incidence of 3.5 per 100 woman-years, 18 months of prescribed follow-up per woman and a maximum of 10% loss to follow-up or early discontinuation.

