#### **8.2.4 Methods for handling missing data**

Primary HIV analyses will censor participants who are lost to follow-up at the date of their last known HIV status. Other missing data will be ignored (i.e. considered missing completely at random), so long as the prevalence of missing outcomes is less than 3%. If the rate of missing data is higher than 3% then multiple imputation methods will be used in estimation and statistical inference of secondary objectives.

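### Exact tests on method continuation ignore follow-up time and stand beside a time-to-event comparison with no rule on which governs; if an arm is closed early they can show a false difference (minor)

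*Protocol*

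**What the plan says.** Method continuation is a secondary endpoint (Protocol 3.5). The paragraph on it in section 8.2.2 sets out three things in this order:

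- Tables: "The study will summarise method continuation in frequency tables including reasons for discontinuation". The examples given are refusal of the assigned method, stopping related to adverse events (AEs), and the participant's request to stop or switch.
- A test: "The study will assess differences across randomisation groups using exact tests conducted at the two-sided 0.05 significance level".
- A time-to-first-event comparison of discontinuation or switching, reported as 95% "confidence intervals for hazard ratios obtained from a stratified PH model", followed by this: "Cumulative probabilities of remaining on assigned method will be estimated based on Kaplan-Meier survival methods".

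No sentence ranks the exact test against the model, gives the exact test a denominator or follow-up window, or calls it descriptive. It is the only significance test named for this endpoint.

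Other parts of the protocol bear on the point:

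- Section 8.1 plans 18 months of follow-up with "a maximum of 10% loss to follow-up or early discontinuation".
- Section 8.2.5 allows a method group to be dropped at an interim analysis while the others go on. Section 9.1.2 adds that follow-up in the remaining arms might be extended.
- The section on missing data says that when more than 3% of outcomes are missing, "multiple imputation methods will be used in estimation and statistical inference of secondary objectives".
- The adverse-event part of 8.2.2 separately compares rates of AEs leading to discontinuation, based on time to first method discontinuation.

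**The concern.** A Fisher-type test on a table of women who did and did not discontinue counts a woman censored while still on her method as a continuer. That is harmless when every arm is observed for the same time. When one arm is observed for less time, its crude discontinuation falls for that reason alone.

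The protocol foresees this situation, because it allows one arm to be dropped while the others continue. Two analyses of the same endpoint could then disagree, and nothing says which to believe. Continuation also informs how the HIV result is read, so a spurious significant difference in continuation could mislead.

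Reason-specific counts have a further problem. Whether a woman is seen to stop for one reason depends on whether she has already stopped for another. The PH model covers first discontinuation or switching from any cause, so it does not address this.

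**Working it through.** The protocol gives no power or error figure for continuation, so there is no planned figure to reproduce. The check asks how often a crude exact test rejects when two arms have the same stopping hazard.

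**Inputs from the protocol.** 2,600 women per arm (Protocol Summary); 18 months of follow-up and 10% loss (8.1); two-sided 0.05 (8.2.2); past 12-month continuation of 50% to 90% (2.6).

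**Assumptions.** Exponential times to stopping and to loss, independent of each other; 12-month continuation of 80% or 65%; arm-specific loss as shown below; in a closed arm, every woman's continuation data end at the stated month. The protocol gives no loss by arm and no closing date.

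**Formula.** With stopping hazard h, loss hazard l (both per year) and follow-up F years, the expected crude proportion discontinued is h/(h+l) × (1 − exp(−(h+l)F)).

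**One arm closed early, 80% continuation, 10% loss in each arm.**

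- h = −ln(0.80) = 0.2231; l = −ln(0.90)/1.5 = 0.0702; h/(h+l) = 0.7606.
- F = 1.5: 0.7606 × (1 − exp(−0.4401)) = 0.271.
- F = 1.25: 0.7606 × (1 − exp(−0.3667)) = 0.234.
- F = 1.0: 0.7606 × (1 − exp(−0.2934)) = 0.193.
- For 18 v 12 months the gap is 0.0774 with a standard error of 0.0117, about 6.6 standard errors, although the hazards are equal.

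**Unequal loss, 18 months in both arms, 80% continuation.** With 5% loss, l = −ln(0.95)/1.5 = 0.0342 and the crude proportion is 0.278, against 0.271 with 10% loss.

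**Rejection rates under identical stopping.** Each setting was simulated 2,000 times. An unstratified log-rank test stood in for the PH comparison.

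| Setting | Fisher exact, 80% / 65% continuation at 12 months | Log-rank, 80% / 65% |
|---|---|---|
| Loss 10% v 10% | 4.7% / 5.5% | 4.8% / 5.8% |
| Loss 5% v 10% | 7.6% / 12.6% | 4.8% / 5.9% |
| Loss 5% v 15% | 20.8% / 34.3% | 4.4% / 4.9% |
| One arm cut to 15 months | 85.6% / 97.3% | 4.6% / 5.0% |
| One arm cut to 12 months | 100% / 100% | 4.7% / 5.2% |

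Across the protocol's full range of 50% to 90% continuation, 5% v 10% loss gives about 6% to 18% false positives by a normal approximation.

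**Competing reasons.** Take one reason with the same hazard in both arms (15% by 18 months if acting alone), and a second reason at 5% in one arm and 20% in the other, with no loss.

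- Hazards: −ln(0.85)/1.5 = 0.1083 for the first reason; 0.0342 and 0.1488 for the second.
- Crude frequency of the first reason: 0.1083/0.1425 × (1 − 0.85 × 0.95) = 0.146, against 0.1083/0.2571 × (1 − 0.85 × 0.80) = 0.135.
- The exact test rejects about 21% of the time, although the hazard for that reason is identical.

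**The case against.** The strongest reply is that the sound analysis is already planned. The same paragraph has a stratified time-to-first-event comparison and Kaplan-Meier estimates, which handle censoring. The strata are presumably sites, as in the primary and pregnancy analyses. This stands: a reader might infer that the protocol's conclusion on continuation rests on the exact tests alone, and it does not. What remains open is which analysis governs when they disagree.

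Other parts of the reply also stand:

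- A reader might infer that site closure (follow-up is "18 months per woman or until closure of the study or study site") or leaving site out of the exact test creates a false difference. Allocation is 1:1:1 within site (6.1), so site closure shortens follow-up in all arms alike, and omitting site does not favour any arm.
- A reader might take the 21% to 34% rates for 5% v 15% loss as the expected size. That split is an assumption and puts one arm above the planned 10% maximum. With equal loss there is no inflation. Women who stop their method are also asked to stay in follow-up (4.6.5).
- The 3% rule on multiple imputation may soften the loss argument. The text does not say whether a woman censored while on her method counts as a missing outcome.
- AE-related stopping has its own rate comparison, and refusal at randomisation involves no follow-up time. Only the remaining reasons depend solely on the crude test.
- Competing reasons do not distort all-cause first discontinuation.
- That the exact tests use crude counts follows from the order of the sentences and is not stated.
- Early closure of an arm may never happen.

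The objection does not remove the main point. A 0.05-level test is stated for a secondary endpoint, nothing limits it to a common window, and it fails in a situation that the protocol itself plans for.

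**Conclusion.** The point holds as a minor one. Read naturally, the exact tests ignore follow-up time and sit beside a sound time-to-event analysis without any order between them.

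The serious case is an arm closed early. If its continuation data end at 12 months rather than 18, identical stopping gives 19.3% v 27.1% and near-certain rejection; at 15 months, false rejection is about 86% at 80% continuation. Unequal loss within the planned maximum is a modest problem, at about 8% to 13% against a nominal 5%. For reasons other than refusal and AEs, the crude comparison also shifts with the competing reasons.

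These sizes rest on exponential times, a two-arm comparison, assumed losses by arm, and closure that cuts every woman in the arm at the same month. Staggered enrolment would spread the follow-up times, and the effect would then depend on how much observation is lost. The protocol does not say whether women in a dropped arm stay under observation; if they did for the full 18 months, this source of bias would not arise.

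**What to change.** In the method-continuation paragraph of section 8.2.2:

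1. Restrict the exact test to refusal of the assigned method at randomisation, or label all other exact tests as descriptive.
2. State that the stratified PH model and the Kaplan-Meier estimates govern inference on continuation, and name site as the stratum.
3. Compare reasons for stopping with cumulative incidence that treats other reasons as competing events, and with site-stratified cause-specific hazard ratios.

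This changes a few sentences. Section 7.1 already has the timing of discontinuation and its reasons recorded, so no new data are needed, and sample size and the primary analysis are untouched.

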### **Adverse events**

AEs that are either serious or result in method discontinuation will be summarised in frequency tables (including both the number of each type of AE and the number of distinct participants ever reporting each type of AE), by system organ class and preferred MedDRA term.

The study will compare rates of SAEs between contraceptive groups using two-sided 95% confidence intervals based on exact Poisson methods. Results will be reported overall, by relatedness, and by geographical region. The analysis will be conducted both according to randomised contraceptive method group and restricted to periods with exposure to each contraceptive method.

The study will similarly compare rates of AEs resulting in method discontinuation between groups using two-sided 95% confidence intervals. This analysis will exclude women who never adopted their assigned method, and will be based on time to first method discontinuation.

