## **6. ASSIGNMENT OF INTERVENTIONS**

### **6.1 Allocation**

Random allocation will use a 1:1:1 allocation to the 3 arms of the trial, stratified by site. Random block sizes between 15 and 30 will be used.

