### **9.2.4 Adverse Event Reporting Requirements**

Sites will monitor AEs starting at randomisation and continuing through the final study visit. Study site staff will document in source documents all AEs reported by or observed in enrolled study participants regardless of severity and presumed relationship to study product. Only AEs that are either a) serious or b) resulting in method discontinuation will be recorded on CRFs. Relevant AEs will be reported to site regulatory authorities according to local guidelines.

Study sites will report all SAEs, including those that may appear to be unrelated to the study interventions (contraceptive method), to the medical monitor at the University of Washington, within 48 hours of becoming aware of the problem. Additional information about these SAEs, including copies of outpatient records, hospitalization summaries, pathology reports, operative reports, and laboratory reports, may be requested. SAEs will be reported to overseeing Institutional Review Boards (IRBs)/Ethics Committees (ECs) according to their policies.

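### SAE rates are to be compared with exact Poisson intervals and no first-event rule; read as all SAEs, these intervals ignore repeat events in the same woman and are too narrow.

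*Protocol*

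**What the plan says.** Comparing SAE rates between the arms is a secondary objective (Protocol, section 3.2). The method is given in section 8.2.2, under Adverse events: "The study will compare rates of SAEs between contraceptive groups using two-sided 95% confidence intervals based on exact Poisson methods". The presentation is also fixed there: "Results will be reported overall, by relatedness, and by geographical region".

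Three other statements bear on how that sentence is read.

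- The frequency tables described just before it give both units: "including both the number of each type of AE and the number of distinct participants ever reporting each type of AE".
- The paragraph that follows it, on AEs leading to discontinuation, limits that analysis to the first occurrence: it "will be based on time to first method discontinuation". The method-continuation analysis in the same section is also on time to first event. The SAE sentence has no such limit.
- Collection runs through the whole of follow-up (section 9.2.4): "Sites will monitor AEs starting at randomisation and continuing through the final study visit".

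**The concern.** An exact Poisson interval assumes independent events, so that the variance of the count equals its mean. That holds closely when each woman contributes at most one event. It fails when the same woman can contribute several, because her events arrive together and the variance of the total exceeds its mean. The interval is then narrower than the data justify.

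Repeats are possible here. SAEs are recorded from randomisation to the final visit, and pregnancy, seroconversion or a change of method does not end follow-up (sections 5.4.9 to 5.4.11). The definition in section 9.2.2 covers hospitalisation, its prolongation and other important medical events.

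At stake is a secondary safety comparison that the DSMB also sees, since section 9.1.2 has it assess non-HIV safety on the secondary endpoints. Intervals that are too narrow make chance differences between arms look firmer than they are.

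**Working it through.** **No figure to reproduce.** The Protocol states no SAE rate, expected count, precision or power. The check is therefore of interval coverage under assumed inputs.

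**Inputs from the Protocol.** 2,600 women per arm, 18 months of follow-up, at most 10% loss. Taking women who are lost to contribute half their time, woman-years per arm = 2,600 × 1.5 × 0.95 = 3,705.

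**Inputs assumed.** SAE rate of 1, 2, 4 or 8 per 100 woman-years, which gives about 37, 74, 148 or 296 SAEs per arm. Mean SAEs per affected woman, m, from 1.0 to 2.0, with a geometric number per affected woman. True rate ratio 1.

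**Formula.** If affected women arise as a Poisson process and each contributes k SAEs, variance/mean of the total = E[k²]/E[k]. For the geometric case this equals 2m − 1, and a correct interval is wider by a factor of √(2m − 1).

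**Result.** Coverage of the exact conditional 95% interval for the rate ratio, 20,000 replicates per cell; the range is over the four SAE rates:

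| m | variance/mean | width factor needed | coverage |
|---|---|---|---|
| 1.00 | 1.0 | 1.00 | 95.5-96.2% |
| 1.05 | 1.1 | 1.05 | 94.3-95.6% |
| 1.10 | 1.2 | 1.10 | 93.4-94.2% |
| 1.20 | 1.4 | 1.18 | 90.5-92.2% |
| 1.35 | 1.7 | 1.30 | 87.3-88.5% |
| 1.50 | 2.0 | 1.41 | 84.3-85.9% |
| 2.00 | 3.0 | 1.73 | 75.1-76.8% |

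**Second repeat model.** A fixed share of affected women has two or three SAEs and the rest have one. Error is 1 − coverage of the same exact interval, for SAE rates of 0.5 to 8 per 100 woman-years and 40,000 replicates.

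| Share with repeats | variance/mean | real error (nominal 5%) |
|---|---|---|
| 5% with two | (0.95 + 0.05×4)/1.05 = 1.10 | about 4-6% |
| 10% with two | (0.90 + 0.10×4)/1.10 = 1.18 | about 5-7% |
| 20% with two | (0.80 + 0.20×4)/1.20 = 1.33 | about 7-8% |
| 40% with two | (0.60 + 0.40×4)/1.40 = 1.57 | about 9-11% |
| 30% with three | (0.70 + 0.30×9)/1.60 = 2.125 | about 14.5-17% |

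The normal approximation 2[1 − Φ(1.96/√φ)], with φ the variance/mean ratio, gives 9.0%, 11.8% and 17.9% for the last three rows. That slightly overstates the error, because the exact interval is itself a little conservative.

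**Site strata.** Randomisation is balanced within site (section 6.1: "Random allocation will use a 1:1:1 allocation to the 3 arms of the trial, stratified by site"). A separate run used 12 sites, 3 SAEs per 100 woman-years, no repeat events and site ignored in the analysis. Coverage was 95.3%, 95.8% and 95.6% with a coefficient of variation of site rates of 0, 0.5 and 1.0. Sums of independent Poisson counts over sites are still Poisson, so omitting site does not narrow the interval.

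**The case against.** The strongest reply is that the Protocol never says all events are counted. Section 8.2 calls itself a summary and leaves detail to the SAP, which may define the numerator as women with a first SAE; the method would then be valid. This stands in part: the all-events reading is an inference. It is still the natural one. The authors distinguish events from women in the tables, then compare rates of SAEs and set first-event rules for the neighbouring analyses but not for this one. The Protocol also goes beyond leaving a detail open, since it names an interval that is valid for only one of the two units.

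A second reply is that the cohort is aged 16-35 with much serious disease excluded, so repeats may be rare. That is fair. The documents give no repeat frequency, and with few repeats the conservatism of the exact interval absorbs most of the loss. Tabulating both events and women would also make repeats visible.

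A third is that no formal decision rests on this interval: the stopping boundaries concern HIV only. This is correct and limits the weight of the point.

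A reader might also infer that the intervals are too narrow because site strata are missing here, while the pregnancy analysis uses hazard ratios "obtained from a PH regression model, stratified by site" and the primary HIV analysis is stratified too. The documents do not support that: with allocation balanced within site, ignoring site leaves coverage at or just above 95%. The difference is one of consistency only.

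**Conclusion.** The point holds conditionally. If the SAE rate counts all events, as the text most naturally reads, the stated exact Poisson intervals take no account of repeat SAEs within a woman and are too narrow. The amount cannot be fixed from the documents. On assumed values it runs from negligible at about 1.05 SAEs per affected woman, through about 3 to 4.5 percentage points of lost coverage at 1.2, to about 10 points at 1.5. If each woman counts once, there is no defect in the interval.

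It would go too far to say that the Protocol specifies event counts, that the SAE data will be over-dispersed by a known amount, or that any particular error rate applies. The importance is modest: this is a secondary safety comparison with no test level or boundary attached. The correction is cheap and needs no new data.

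**What to change.** In section 8.2.2 (or the SAP, as a documented clarification), name the unit and match the interval to it:

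- For the rate of women with a first SAE, with time at risk ending at that event, keep the exact Poisson interval.
- For the rate of all SAEs, use Poisson regression with woman-level robust variance, or negative-binomial regression, with woman-years as offset.

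Site may be added as a stratum or model term in line with the HIV, pregnancy and continuation analyses; this is optional and is not needed to correct the width.

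The cost is a sentence or two of text, standard software and somewhat wider all-event intervals: about 1.10 times at 1.1 SAEs per affected woman, 1.18 times at 1.2 and 1.41 times at 1.5, under the geometric assumption. Events and woman identifiers are already needed for the planned tables, so no further data collection is required.

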Fears and misbeliefs contribute to method discontinuation in many women requesting IUD removal [49], and structured and extensive counselling may help mitigate these fears [50]. In one randomised trial in Mexico, women who received pre-treatment, structured information about DMPA were more likely to continue the method than were women who received routine counselling[51]. Recent studies have found that method continuation can be improved with careful planning and counselling. In the largest cohort study of hormonal contraception and HIV study to date, contraceptive continuation rates at 1 year were 78% for DMPA users [52]. In a recent large US cohort study, high continuation rates were seen among young women beginning long-acting reversible contraceptive methods including IUDs and implants, with use of DMPA, IUDs, and implants also associated with very low failure rates (<0.3 pregnancies per 100 person-years)[53, 54]. In this study, designed to focus on improving use of long-acting methods, 12-month continuation rates were: LNG intrauterine system (88%), copper IUD (84%), implant (83%), and DMPA (57%)[54]. Lastly, among women who were not using effective contraception prior to enrolling in the recent FEM-PrEP HIV trial but who chose to use an injectable method (DMPA or NET-En) to fulfil the study's contraceptive use requirement, 82% continued to use their injectable for an average of 9 months of study participation, despite switching to other methods being permitted per protocol (88% of existing injectable users so continued)[55]. In summary, these studies demonstrate that in structured research settings in sub-Saharan Africa continuation rates for DMPA can range from 40 to 85%, and continuation rates for implants and copper IUD can range from 68% to 96%.

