In the proposed ECHO trial, potential study participants will be carefully assessed and counselled prior to randomisation, to ensure that they are willing to be randomised, willing to defer pregnancy and to use their assigned method for their duration of study participation. The length of study follow-up (18 months or until closure of the study or a study site) was chosen because women commonly use longer acting contraceptives for at least this length of time, and it would ensure the required number of participants while also not placing undue burdens on either women or the sites. Intensive, on-going counselling will be provided to study participants about the side effects associated with each of the three contraceptive methods, because method discontinuation is most often due to side effects, especially those that are unanticipated. Finally, each participant will be scheduled for a follow-up visit at one month after her randomisation to focus on early side effects/tolerability to assist with method start-up symptoms that often abate. Obtaining the best possible contraceptive continuation rates will be addressed through following 'best practices' strategies reported in previous studies as well as linkages with family planning programs to help women transition after the study.

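### AE-related method discontinuation is compared as a constant rate, although its hazard may fall over time and other stopping may differ by arm; a site-stratified cause-specific PH model with cumulative incidence would be safer

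*Protocol*

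**What the plan says.** AEs resulting in method discontinuation are one of four secondary endpoints (Protocol section 3.5). Section 8.2.2, Adverse events, sets the analysis in two steps. For serious AEs: "The study will compare rates of SAEs between contraceptive groups using two-sided 95% confidence intervals based on exact Poisson methods". For AEs leading to discontinuation: "The study will similarly compare rates of AEs resulting in method discontinuation between groups using two-sided 95% confidence intervals". It adds: "This analysis will exclude women who never adopted their assigned method, and will be based on time to first method discontinuation". The second comparison names no model of its own. That it is a Poisson rate comparison rests on the word for likeness that links it to the first.

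The neighbouring paragraph of section 8.2.2, Contraceptive method continuation, treats stopping for any reason differently. Time to first stop or switch is compared "using two-sided, 95% confidence intervals for hazard ratios obtained from a stratified PH model", with Kaplan-Meier curves for remaining on method. It also plans a descriptive step, "The study will summarise method continuation in frequency tables including reasons for discontinuation", with exact tests across arms.

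Section 2.6 explains that the one-month visit is there "to assist with method start-up symptoms that often abate". It summarises continuation in structured research settings in sub-Saharan Africa as 40-85% for DMPA and 68-96% for implants and copper IUD. Randomisation is stratified by site (section 6.1).

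**The concern.** A woman who stops her method by choice, through pregnancy or by switching can no longer have an AE-related first discontinuation. Her woman-time ends without an event. If AE-related stopping is commoner soon after initiation, an arm with more stopping for other reasons contributes a larger share of early, higher-hazard woman-time. Its average rate rises even when the AE-stopping hazard is the same in both arms at every time point.

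Two things are at stake for this endpoint. The interval can exclude a ratio of 1 when the hazards are equal. And a rate alone can rank the arms differently from the share of women who stop because of an AE, which is what a counsellor would want to know.

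**Working it through.** The protocol states no figure for this endpoint to reproduce; its sizing concerns HIV infection only. The check asks how large the distortion could be.

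**Inputs from the Protocol.** 2,600 women per arm and 18 months of follow-up (Summary, section 8.1). 12-month continuation pairs from section 2.6: 57% DMPA against 83% implant (a US cohort); 80% DMPA against 85% IUD and 65% against 68% (two randomised comparisons); and 40% as the low end for DMPA.

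**Assumptions, not in the Protocol.** The AE-stopping hazard is identical in both arms: h1 = 0.20 per year in months 0-3 and h2 = 0.05 per year after. The hazard g of stopping for other reasons is constant and carries the whole continuation gap. No other losses.

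**Formulas (years).**
- g = -ln(12-month continuation) - (0.25·h1 + 0.75·h2)
- Early woman-years per woman: P1 = (1 - S3)/(h1 + g), with S3 = exp(-0.25·(h1 + g))
- Later: P2 = S3·(1 - exp(-1.25·(h2 + g)))/(h2 + g)
- Rate = (h1·P1 + h2·P2)/(P1 + P2). The numerator is also the 18-month cumulative incidence of AE-related stopping.
- SE of the log rate ratio = sqrt(1/events1 + 1/events2)

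**57% against 83%.** The AE part of the 12-month cumulative hazard is 0.25·0.20 + 0.75·0.05 = 0.0875.

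| | DMPA (57%) | Implant (83%) |
|---|---|---|
| g | 0.5621 - 0.0875 = 0.4746 | 0.1863 - 0.0875 = 0.0988 |
| P1, P2 | 0.2301, 0.7745 | 0.2409, 1.0585 |
| Share of woman-time in months 0-3 | 22.9% | 18.5% |
| Events; woman-years | 220; 2,612 | 263; 3,378 |
| Rate per 100 woman-years | 8.44 | 7.78 |
| Cumulative incidence, 18 months | 8.5% | 10.1% |

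The ratio is 8.44/7.78 = 1.084, where the true hazard ratio is 1.00. SE = sqrt(1/220 + 1/263) = 0.091, so ln(1.084)/0.091 = 0.88. A two-sided 5% comparison centred 0.88 SE from zero rejects about 14% of the time. The rate is higher on DMPA while the share of women who stop for an AE is lower.

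**Other settings, same formulas.**

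| 12-month continuation | Rate ratio | SEs from 1 | False-positive rate |
|---|---|---|---|
| 80% against 85% | 1.013 | 0.15 | about 5% |
| 65% against 68% | 1.010 | 0.11 | about 5% |
| 40% against 83% | 1.17 | 1.6 | about 38% |
| 57% against 83%, h1 from 0.15 to 0.30 | 1.06 to 1.11 | 0.6 to 1.3 | about 10% to 26% |
| 57% against 83%, flat hazard 0.10 | 1.00 | 0 | 5% |

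In the flat case the rates agree, yet cumulative incidence is still 10.1% against 13.1%. With a rising hazard (0.005 per month, then 0.010), 10% loss and continuation of 40% against 85%, the ratio is 0.95, so the bias changes direction.

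**Does the alternative work?** Trials were simulated with equal AE-stopping hazards and non-AE 12-month continuation of 96% against 68% (1,500 per setting). For early hazards 1, 2, 4 and 8 times the later one, the exact Poisson comparison rejected in 5%, 7%, 15% and 33%. A log-rank comparison with the same censoring gave hazard ratios of 1.00 and rejected in 5-6% throughout.

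**The case against.** The case against has force, and most of it narrows the point.

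- **The Poisson reading is inferred.** The sentence does not name the method, section 8.2 calls itself a summary, and detail may sit in the SAP. This stands as a caution. But the text does carry a stated method across, and the only alternative nearby is the PH model that it does not invoke.
- **The hazard shape is assumed.** Section 2.6 speaks of symptoms that abate, not of stops concentrated in months 0-3. Section 2.4.2 places implant bleeding problems across the whole first year. This stands.
- **The gap in non-AE stopping is assumed.** The continuation figures cover stopping for any reason, and section 2.6 says that side effects are the commonest cause. A large gap could then be mostly a true AE difference. The 57%/83% pair is not randomised, the two close randomised comparisons give a ratio of about 1.01, and a Zambian trial shows the opposite order (about 95% hormonal against 77% IUD). So neither the size nor the direction of the bias is established.
- **AE-related stops are already tabulated and tested.** The reasons tables come with exact tests, so this is not the only planned comparison between arms. It is the only planned comparison of rates.

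A reader might also infer that censoring at non-AE stops is itself wrong. It is not: a woman off her method cannot stop it, and the recommended model censors in the same way. Nor are arms with more stopping observed mainly in the early period: in the worked case the shares of woman-time in months 0-3 are 23% and 19%.

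**Conclusion.** The point holds in limited form. The fault is a constant-rate comparison that makes no provision for site, on a time scale where the hazard may well fall and stopping for other reasons may well differ. Under the assumed front-loaded hazard, the ratio is distorted by about 1% when continuation is close, 8% at 57% against 83%, and 17% at 40% against 83%. There is no distortion if the hazard is flat. All of these figures assume that non-AE stopping is independent of AE risk; dependence would add a bias that neither method removes.

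The documents do not support a prediction that DMPA, or any other arm, will show a false safety excess. They support only the statement that the chosen comparison is open to one, while a better method already stands in the adjoining paragraph. This concerns one secondary safety endpoint and leaves the primary HIV analysis untouched.

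**What to change.** In section 8.2.2, Adverse events, replace the comparison of AE-related discontinuation rates with two statements:

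1. Time to AE-related first discontinuation is compared between arms by a cause-specific PH model stratified by site, with 95% intervals for the hazard ratios. Follow-up is censored at first discontinuation for any other reason. This matches the stratified PH model already planned for stopping of any kind.
2. The Aalen-Johansen cumulative incidence of AE-related discontinuation is reported by arm at 12 and 18 months, with discontinuation for other reasons as the competing event.

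The exact Poisson method can stay for serious AEs.

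The cost is a change of wording and a few lines of code, since timing and reasons for discontinuation are already recorded (section 7.1). The drawbacks are two summaries in place of one rate, and asymptotic rather than exact intervals. With event counts like those assumed above (220 and 263), the loss of exactness would matter little.
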